### Intervention description {11a}

Intervention group: the application of the technique will be carried out in a single moment and will be applied with the patient in supine decubitus with 30° elevation of head and trunk, the rapid chest compression technique will be applied once in the expiratory time of each 3 respiratory cycles during 5 min by a physiotherapist. Safety monitoring of heart rate, blood pressure, intracranial pressure, peripheral oxygen saturation, and cerebral perfusion pressure will be performed by the clinical team and the principal investigator. The intervention will stop if reached some of the safety values presented below or when the clinical team considers.

Control group: the technique will be performed in a single moment and will be applied with the patient in supine decubitus with 30° elevation of head and trunk. The passive mobilization technique of the right first metatarsophalangeal joint will be applied to the available range of flexion-extension, performing 15 repetitions per minute and for 5 min by a physiotherapist. Safety monitoring of heart rate, blood pressure, intracranial pressure, peripheral oxygen saturation, and cerebral perfusion pressure will be performed by the clinical team and the principal investigator. The intervention will stop if reached some of the safety values presented below or when the clinical team considers.

### Criteria for discontinuing or modifying allocated interventions {11b}

The interventions will stop if reached some of the safety values presented below or when the clinical team considers [11, 22, 23].

**Table Tabb:** 

Safety limits	
40 bpm < **Heart rate** < 120 bpm	
60 mmHg < **Mean arterial pressure** < 110 mmHg	
− 10 mmHg < **Intracranial pressure** < 30 mmHg	
90% < **Oxygen saturation**	
50 mmHg < **Cerebral perfusion pressure**	

The rescue plan is the usual at our ICU to manage the pathological increases in the ICP: open drainage if exists, increase sedation, apply relaxation medicines and hypertonic solution, this in a step-by-step approach.

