At present, there are no randomized clinical trials that have studied the effect of the manual rapid chest compression technique alone on intracranial pressure and that try to relate its behavior with the different kinds of acute brain injuries. Therefore, we believe that it is necessary to investigate the effects of the technique with the highest possible methodological rigor and quality [10–12].

We propose this study, trying to control as many variables as possible and studying the effects of a single technique, in order to provide methodologically sound conclusions.

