#### Objectives

##### Primary objective

To determine the effects of the rapid chest compression technique on intracranial pressure in patients on invasive mechanical ventilation with severe acute brain injury.

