#### Intracranial pressure

The intracranial pressure (mmHg) data will be recorded 1 h prior to the intervention, due to the change in mechanical ventilation mode, 30 min prior, 5 min prior, at the beginning of the intervention and every minute since the beginning, 5 and 30 min since the end with the continuous intracranial pressure monitoring system from Integra® Camino®.

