## Statistical methods

### Statistical methods for primary and secondary outcomes {20a}

A descriptive analysis of the collected values of the variables under study will be carried out, studying the measures of central tendency. Normal distributions will show mean and standard deviation and median and interquartile range in case of non-observation of normal distribution. The normality of the samples will be verified with the Kolmogorov-Smirnov test.

The verification of the hypothesis under study will be assessed using Student’s *T* test for independent samples in case of normality of the sample and by the *U* Mann-Whitney test otherwise.

A multiple linear regression analysis will be performed: considering as a dependent variable the intracranial pressure differences, difference or gain of expiratory flow and between the covariates, the type of technique, the pressure applied in the technique under study, the type of brain injury, blood gases changes, age, and sex.

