## Discussion

Nowadays, the chest physiotherapy techniques are applied with several restrictions because of their effect in the intracranial pressure values, at least as referred to in several publications [5–12].

The main problem that we observe in almost every publication about the chest physiotherapy techniques in acute cerebral injured patients is that they usually include a protocol that has secretion suction at the end without separation of the effects. It’s known that the suction has clear reflex effects that increase the ICP and MAP even when patients are sedated, as shown in a recent study from Singh et al. (2018) [12] where they studied different drug effects on intracranial pressure, applying chest percussion and suctioning.

We believe, for our clinical experience and some publications that when adequately applied, rapid chest compression is safe and patients can benefit from its use, because invasive mechanical ventilation increases the risk of respiratory complications, making the management of acute cerebral injuries more complex and its influence is unknown on the outcomes [1–5, 10, 12].

In our trial, we intend to control the larger number of possible interactions to avoid results that can be affected by collateral techniques.

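### If ICP-lowering rescue starts before the +5 or +30 min reading, the planned arm comparison uses a treated value and can understate harm from compression

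*Protocol article*

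**What the plan says.** **Stopping and rescue.** The protocol article, under Criteria for discontinuing or modifying allocated interventions {11b}, states: "The interventions will stop if reached some of the safety values presented below or when the clinical team considers". The safety limits include an upper ICP limit of 30 mmHg and a lower cerebral perfusion pressure (CPP) limit of 50 mmHg, alongside heart rate, mean arterial pressure (MAP) and oxygen saturation. Below the table, the rescue for pathological ICP increases is the unit's usual care: "open drainage if exists, increase sedation, apply relaxation medicines and hypertonic solution, this in a step-by-step approach". No ICP threshold or start time for rescue is given.

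**Readings.** Under Intracranial pressure, the follow-up readings are taken "at the beginning of the intervention and every minute since the beginning, 5 and 30 min since the end". Nothing ends or flags these readings after a stop or a rescue. The only rule that removes a patient concerns unblinding (section {17b}).

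**Analysis.** Section {20a} says: "The verification of the hypothesis under study will be assessed using" a two-sample t test, or Mann-Whitney if the data are not normal. The regression covariates are "the type of technique, the pressure applied in the technique under study, the type of brain injury, blood gases changes, age, and sex". Rescue is not listed.

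**Sizing and purpose.** Sample size {14} takes its means from an earlier study at baseline and 30 min after physiotherapy. The primary objective is "To determine the effects of the rapid chest compression technique on intracranial pressure", and the Discussion paragraph of the Abstract says that the study is to show whether the technique is safe.

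**The concern.** Rescue is triggered by the main outcome, and every step of it is meant to lower that outcome. If compression raises ICP enough in some patients to call for rescue, their later readings are the ones brought down by treatment. Compared as they stand, those readings make the compression arm look closer to control than the technique alone would have left it.

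The direction matters because this is a safety question. A result near no change is the one that would support calling the technique safe. With 25 patients per arm, a few treated values can carry weight in a late comparison.

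**Working it through.** **1. The plan's own figure.** Inputs from Sample size {14}: limit 2.0 mmHg, SD 2.5 mmHg (the ICP 10–20 stratum), 80% power, 95% confidence.

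n per arm = 2 × [(1.960 + 0.842) × 2.5 / 2.0]² = 24.5, rounded up to 25.

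The stated 25 per arm reproduces. The means given beside that SD are for baseline and 30 min after physiotherapy, so the sizing points to a late reading, although no primary time point is named.

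**2. Which readings can be affected.**
- Readings during application, up to the stop: unaffected.
- +5 min: affected only if rescue has started by then. A stepwise rescue may start later.
- +30 min: the more exposed of the two.
- A stop for heart rate, MAP or saturation need not bring ICP-lowering treatment.

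**3. Direction.** Let f be the share of the compression arm rescued before the reading. Let r be the lowering at that reading relative to what it would have been untreated. With no rescue among controls:

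observed mean difference = untreated mean difference − f × r.

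For r above 0 the shift is toward lower ICP under compression. The protocol gives neither f nor r. If ICP would have settled by itself once compression stopped, r is near 0 and so is the bias. Rescue among controls would partly offset it.

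**4. How likely rescue is through the 30 mmHg limit.**
- Rise needed: 30 − 20 = 10 mmHg from the entry ceiling (so more than 10); 30 − 13.7 = 16.3 and 30 − 6.9 = 23.1 mmHg from the two sizing baselines.
- Assume baseline 13.7, SD 2.5 and a uniform rise. Rise 10: z = (30 − 23.7)/2.5 = 2.52, p = 0.0059, × 25 = 0.15 patients. Rise 12: z = (30 − 25.7)/2.5 = 1.72, p = 0.0427, × 25 = 1.07 patients.

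Rescue by this route should be uncommon. It is not the only route, since rescue is tied to pathological increases with no stated threshold. A stop can also come from CPP: with MAP 66 and ICP 15, CPP is 51, and a 1 mmHg ICP rise at constant MAP reaches the limit of 50. Such a stop need not lead to rescue.

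**5. How far a worst-rank analysis would move the result.** Suppose a rescued patient's observed value lies at control percentile q. Ranking that patient worst raises the probability that a compression-arm ICP exceeds a control ICP by (1 − q)/25:
- q = 0.25: 0.75/25 = 0.03
- q = 0.50: 0.50/25 = 0.02
- q = 0.75: 0.25/25 = 0.01

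One to three rescues (assumed) give 1 × 0.01 = 0.01 to 3 × 0.03 = 0.09. For scale, a 2.0 mmHg shift moves the same probability by Φ(2/(2.0√2)) − 0.5 = 0.260 with SD 2.0, or Φ(2/(2.5√2)) − 0.5 = 0.214 with SD 2.5. The range is therefore 0.01/0.260 = 4% to 0.09/0.214 = 42% of that movement. It measures what the scoring rule does under assumed rescue counts. It does not measure the bias.

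**The case against.** **The protocol never says that post-rescue values are used as untreated.** True. That follows from a plain test and a covariate list without rescue, and an analysis plan not shown here may set a rule. So the point is not that a rule is missing. The documented rescue, the continued readings and the plain comparison combine badly, and the start time of rescue has to be captured at the bedside because no later analysis rule can restore it.

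**Observed values regardless of rescue answer a legitimate question.** They describe the technique together with usual care, and both arms share the same stopping rule. This stands, and it is why the planned test should stay. Such a comparison does not by itself show that the technique leaves ICP unchanged.

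**A reader might infer that the plan contradicts its own aims.** The Background speaks of "trying to control as many variables as possible and studying the effects of a single technique", and the Discussion says "we intend to control the larger number of possible interactions to avoid results that can be affected by collateral techniques". In context these set the trial apart from studies that bundled chest physiotherapy with secretion suction. They do not promise an estimate free of emergency treatment, so the contradiction is not supported.

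**A reader might take 0.01–0.09 as the size of the bias.** It would be that only if the untreated late ICP of each rescued patient had been worse than every other patient's. The Background describes the pressure effect as momentary, and the technique stops at the limit, so late ICP could have recovered unaided. The upper end also needs three rescues. On the uniform-rise model that is 3/25 = 0.12, z about 1.175, a rise of about 30 − 1.175 × 2.5 − 13.7 = 13.4 mmHg, which the minute-by-minute readings would show plainly.

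**Conclusion.** The concern holds in a limited form. When ICP-lowering rescue starts before the +5 or +30 min reading, the comparison in section {20a} uses a treated value and can understate harm from compression. This includes the 30 min point on which the sizing draws.

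The direction assumes that rescue lowers ICP below its untreated course and falls more often on the compression arm. The size cannot be derived, because the protocol gives neither a rescue rate nor a rescue effect, and rescue is probably uncommon. The documents do not support saying that the trial's main result will be biased, or by how much. The change is still worth making before late data are compared, because it is cheap and because the error would favour the reassuring conclusion.

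**What to change.** 1. Record the time and ICP at any stop, and the start time of any ICP-lowering rescue.
2. Report ICP-related safety stops and rescues by arm as a safety outcome, next to the ICP comparison.
3. Keep the planned test on observed values. For any +5 or +30 min comparison, add a pre-specified sensitivity analysis (Mann-Whitney) that ranks patients rescued before that reading as worst.
4. Report the highest ICP change from the 5-min-prior reading during application, up to stop or rescue.
5. State that the technique will not be called safe on late observed values alone.

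Adding rescue to the regression is not a substitute, since it is a consequence of the outcome under study.

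Stopping limits, rescue steps and sample size stay unchanged. The cost is about two form fields (the form is not shown, so they may already exist), a little more analysis, and a possibly less favourable result for compression. The ICP readings themselves are already planned.

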### Outcomes {12}

The data about patient’s clinical situation and demographics will be collected directly from the clinical history. The main and secondary outcomes will be collected as described below:

#### Intracranial pressure

The intracranial pressure (mmHg) data will be recorded 1 h prior to the intervention, due to the change in mechanical ventilation mode, 30 min prior, 5 min prior, at the beginning of the intervention and every minute since the beginning, 5 and 30 min since the end with the continuous intracranial pressure monitoring system from Integra® Camino®.

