Patients with acute brain damage usually present respiratory complications associated with invasive mechanical ventilation and therefore could benefit from respiratory physiotherapy. However, the application of respiratory physiotherapy techniques in these patients could be associated with an increase in intracranial pressure [7–10, 12]. The maneuvers of respiratory physiotherapy can momentarily increase intrathoracic pressure, decreasing venous return and increasing intracranial pressure [6].

The intrathoracic pressure is directly related to the alveolar pressure and the manual rapid chest compression technique can increase momentarily the alveolar pressure. So, any technique that aims to increase the expiratory air flow must do it in a rapid way to avoid major intracranial pressure increases [6, 13–17].

According to the bibliography, the increase in intracranial pressure is a contraindication for the application of some techniques in patients with acute brain injury since it can cause a decrease in cerebral perfusion pressure if it is sustained over time or if it is not accompanied of a rise in the mean arterial pressure. The lowering of cerebral perfusion pressure leads to associated damage in the control mechanisms of blood supply in areas of penumbra, which will be responsible for part of the neuroplasticity in the recovery phases of acute brain injuries, with all its implications [10, 12, 18–20].

It is important to mention that different brain lesions may have different behaviors in terms of intracranial pressure and may present higher intervention risks [18].

Cerebral lesions with a hemorrhagic component imply a more aggressive control of the mean arterial pressure and intracranial pressure and may present extreme complications with punctual rises, as these pressure rises may cause an increase in hemorrhagic lesions due to fragility. The ischemic brain lesions may have an inverse behavior since decreases in mean arterial pressure or increases in intracranial pressure can lead to decreases in the cerebral perfusion pressure and make the penumbra areas suffer [18–21].

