### Sample size {14}

To obtain the sample size needed for this study we worked with the software Ene 3.0 and based the estimations on the changes in intracranial pressure with the techniques performed in the study by Thiesen et al. (2005), in which the mean of baseline measures (equivalent to the control group) was 6.9 mmHg, mean in the experimental group was 7.2 mmHg 30 mins post-physiotherapy and joint standard deviation was 2.0 mmHg in patients with ICP 0–10 mm and the mean of baseline measures (equivalent to the control group) was 13.7 mmHg, mean in the experimental group was 12.7 mmHg 30 mins post-physiotherapy and joint standard deviation was 2.5 mmHg in patients with ICP 10–20 mmHg.

With a power of 80% and to detect that the difference of means is equal to the equivalence limit by means of a *T*-Student test for two independent samples, assuming that the equivalence limit is 2.0 mmHg and a level of confidence of 95%, we obtained a sample size of 25 patients in each group: control and experimental. The total number is 50 subjects for this RCT.

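### Intracranial pressure is recorded at minute marks with no peak or window summary, so a brief rise at each compression, one of the two hazards the protocol names, is missed or diluted

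*Protocol article*

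**What the plan says.** **Hazard.** Background and rationale {6a} of the protocol article gives the mechanism: "The maneuvers of respiratory physiotherapy can momentarily increase intrathoracic pressure, decreasing venous return and increasing intracranial pressure". It names two kinds of harm. Haemorrhagic lesions "may present extreme complications with punctual rises". Raised ICP is also a concern because "it can cause a decrease in cerebral perfusion pressure if it is sustained over time".

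**Exposure.** Under Intervention description {11a}, the compression "will be applied once in the expiratory time of each 3 respiratory cycles during 5 min".

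**Measurement.** Under Outcomes {12}, Intracranial pressure, values are taken at 60, 30 and 5 minutes before, then "at the beginning of the intervention and every minute since the beginning, 5 and 30 min since the end". The device named there records without interruption: the values are obtained "with the continuous intracranial pressure monitoring system from Integra® Camino". No peak, window or average is named. For expiratory peak flow, the same section has every peak in a 30-second period checked and the best one kept.

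**Planning.** Sample size {14} draws on an earlier uncontrolled study. In its lower-ICP stratum the "mean in the experimental group was 7.2 mmHg 30 mins post-physiotherapy", and the higher stratum uses the same time point.

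**Analysis.** Statistical methods {20a} gives one two-group test and a regression on ICP differences. Neither is tied to a time.

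**Stopping and rescue.** The safety table under {11b} sets an upper ICP limit of 30 mmHg. Usual care for pathological rises is "open drainage if exists, increase sedation, apply relaxation medicines and hypertonic solution, this in a step-by-step approach".

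**The concern.** The trial asks whether the technique is safe for ICP. One of the protocol's two stated hazards is a rise lasting about as long as a compressed expiration and recurring every third breath. Readings a minute apart are not linked to those compressions. If each is an instantaneous value, it catches a rise only by chance. If it is an average on the monitor, the rise is diluted. The protocol solved the same problem for flow by keeping the best value in a window, but did not do so for ICP.

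The only outcome time used in planning is 30 minutes after treatment, when a momentary rise would be over. Readings at 5 and 30 minutes may also follow ICP-lowering treatment in patients who were stopped. A technique that raises ICP briefly at each compression could therefore be reported as having little effect. A later analysis plan could fix the time point, but it could not recover peaks that were never stored.

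**Working it through.** **1. Reproduce the planned size.** Inputs from Sample size {14}: limit 2.0 mmHg, SD 2.5 mmHg (ICP 10–20 stratum), 80% power, 95% confidence.

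n per group = 2 × [SD × (1.960 + 0.842) / limit]² = 2 × [2.5 × 2.802 / 2.0]² = 24.5, so 25.

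The stated 25 per group reproduces, with power 80.7% by the normal approximation. The SD behind it belongs to a 30-minute post-treatment value. The 2.0 mmHg is a chosen limit. The 30-minute differences in the source (7.2 − 6.9 = +0.3 and 12.7 − 13.7 = −1.0 mmHg) do not drive n.

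**2. Share of the application spent in a rise.** Respiratory rate and rise duration are not in the protocol. Assume 12–20 breaths/min and a rise of 1–3 s per compression.

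f = (rate / 3) × duration / 60

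**3. Chance that one patient's five minute readings all miss.** Assume instantaneous readings unsynchronised with the compressions.

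P(no hit) = (1 − f)⁵

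| Rate (/min) | Rise (s) | f | P(no hit in 5) |
|---|---|---|---|
| 12 | 1 | 0.067 | 0.71 |
| 15 | 1 | 0.083 | 0.65 |
| 15 | 2 | 0.167 | 0.40 |
| 15 | 3 | 0.250 | 0.24 |
| 20 | 3 | 0.333 | 0.13 |
| 15 | 5 | 0.417 | 0.07 |

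The last row lies outside the assumed range and shows that longer rises are seldom missed.

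**4. Dilution of the group mean.** At 15 breaths/min and 2 s, the expected shift in one reading is f × rise: 0.167 × 5 = 0.83 mmHg, or 0.167 × 10 = 1.67 mmHg.

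**5. Power for one reading during the procedure.** With SD 2.5 and 25 per group, treating the diluted shift as constant gives power of about 22% (5 mmHg rise) and 65% (10 mmHg rise). That is too favourable, because readings that hit or miss a rise add variance rise² × f × (1 − f).

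- 10 mmHg rise: variance in the compression group 6.25 + 100 × 0.139 = 20.1; standard error of the difference √[(20.1 + 6.25)/25] = 1.03; ratio 1.67/1.03 = 1.62. A simulated t test gives 33% power.
- 5 mmHg rise: variance 6.25 + 25 × 0.139 = 9.72; standard error √[(9.72 + 6.25)/25] = 0.80; ratio 0.83/0.80 = 1.04. Simulation gives 17%.

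**6. Across the whole group.** With f = 0.083 and 25 × 5 = 125 readings, the expected number of hits is 125 × 0.083 = 10.4, and the chance of none is 0.917¹²⁵ ≈ 0.00002. The group therefore almost surely contains some hits. The loss lies in dilution and added noise, and in each patient's peak going unrecorded.

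**7. Would a window mean cure this?** Its expected shift is the same f × rise. It removes the sampling noise of step 5 but not the dilution of step 4. Only a peak measures the height of a brief rise.

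**The case against.** - **ICP is recorded during the procedure, and sustained rises are a stated hazard too.** This stands. Minute readings with +5 and +30 minutes suit a sustained or cumulative rise, so the gap concerns brief rises only.
- **The protocol does not say that the readings are instantaneous.** This stands, and the probabilities above depend on it. A monitor average would still dilute a brief peak. Only a window maximum would capture it, and none is named.
- **Bedside staff watch ICP and stop at the limit.** This is true, and it bounds the illustration. From the planning baselines of 6.9 and 13.7 mmHg, a 24 mmHg rise would reach 30.9 and 37.7 mmHg, above the 30 mmHg limit. Very large unnoticed rises are therefore not credible. Smaller ones are, and safety observation is not made outcome data.
- **Time point, multiplicity and post-rescue handling may sit in an analysis plan.** This is fair. A reader might infer that seven separate tests are planned, with an inflated error rate, but the document plans one test and does not say on which reading.
- **Rescue may not distort the later readings.** A reader might infer that every patient crossing a limit is rescued and then looks best at 30 minutes. The document says that the intervention stops, and describes stepwise usual care for pathological rises. Distortion is possible but not established.
- **Planning on 30-minute figures does not make 30 minutes the primary time.** Correct. Only the means and SDs come from there.

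**Conclusion.** The point holds for brief rises. The protocol names them as dangerous, delivers a stimulus that could cause them every third breath, and records ICP in a way that misses or dilutes them. On the assumed 12–20 breaths/min, 1–3 s rises and instantaneous unsynchronised readings, a patient's five minute readings all miss with probability of about 13–71%. At 15 breaths/min and 2 s, a 10 mmHg rise at every compression shifts one reading by 1.67 mmHg on average and is detected about a third of the time.

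A reader might infer that the trial cannot detect any ICP effect, or that its size is wrong because of the 30-minute source. Neither follows. Sustained rises are visible, and 25 per group reproduces from the stated inputs. What is unsupported is a conclusion of safety against brief peaks. This should be changed before recruitment, because data collection determines it.

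**What to change.** 1. From the continuous monitor already in use, record peak ICP and mean ICP over the 5-minute application and over a matched 5-minute pre-intervention window, in both arms. Window peaks follow the protocol's own practice for flow.
2. Base the primary comparison on the application window, adjusted for the same pre-intervention measure. Report peak beside mean, as co-primary or first secondary outcome, because the mean alone still dilutes brief rises. If they are co-primary, state how the error rate is shared.
3. Keep the +5 and +30 minute values as measures of persistence.
4. Flag readings taken after a stop or rescue, and report stops and rescue by arm beside the primary result.

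**Cost.** The trace must be exported, or window peaks logged at the bedside; the protocol does not say whether the trace is stored, so this needs checking. The documents give no SD for peak or window-mean ICP, so no revised sample size can be computed from them. The 2.5 mmHg must be labelled an assumption for the new measures.
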